**Figure 1 f1:**
[figure not shown]
SPIRIT 2025 diagram of the schedule of enrollment, interventions, and assessments for the Time to Move Randomized Crossover Trial, the University of Tennessee Medical Center, Knoxville, Tennessee, USA.

Randomization is blocked (block size 4) and stratified by GGI and GDM. The allocation is concealed by a colleague who is not a member of the study team. The study investigators are blinded to treatment assignment: the analytic programmer will present all results by treatment A, B, and C until the conclusion of the trial (i.e., the investigators will remain blinded through the drafting of the study’s *Results* section and then be unblinded to write the *Discussion* and finalize the study).

### Conditions

2.4

For PA, participants are instructed to perform 30 min of moderate-intensity walking or stepping (i.e., walking in place or around a small area) (34) following the respective meal. Moderate-intensity PA is described as activities during which you can comfortably talk but not sing. Moderate-intensity walking or stepping is described as a cadence of approximately 100 steps per minute. Well-known songs at 100 beats per minute, such as the Bee Gee’s *Stayin Alive* and Beyonce’s *Crazy in Love*, are recommended to help participants walk or step at 100 steps per minute (35). On days they are assigned morning PA, participants are instructed to walk or step between 5 a.m. and 9 a.m. and to begin their PA 30 min–40 min after the start of their breakfast. On days they are assigned evening PA, they are to walk or step between 4 p.m. and 8 p.m. and begin 30 min–40 min after the start of their dinner. Adherence to PA is defined as completing at least 80% of the assigned PA during the assigned window (i.e., 24 min or more of the continuous walk/run activity type, as detected by the device (see Section *Device-assessed physical activity*), during the assigned timeframe). Participants are instructed to not perform any additional PA intentionally for health or wellness outside of the assigned (by day and time range) walking or stepping for the duration of the study.

A personalized calendar outlining each day’s PA (or no PA) assignment and data collection activities (described below) and their time of day in a checklist format is provided at the Study Visit. The study staff also review a handout on ‘Keeping it safe’ during PA in pregnancy with the participant and develop an Action Plan for their PA. The Action Plan includes specific details on the times they will perform their PA (within the assigned ranges/days), the location(s) where they will perform their PA, the type of PA (i.e., walking or stepping), a strategy for maintaining PA at least a moderate intensity throughout their sessions (e.g., using either the ‘talk test’ or walking to a 100 beats per minute song), and potentially, with whom they will do their PA or what they will listen to/watch during their sessions. Participants are offered personalized encouraging text message reminders for their PA. To the extent possible, roles at the Study Visit are split: one member of the study team works with the participant on their PA Action Plan and another member of the team reviews the data collection procedures.

### Data collection

2.5

Data are collected by trained study staff at the Study Visits (e.g., weight using a wireless WYZE scale and height using a Seca stadiometer) and abstracted from the electronic health records (i.e., pre-pregnancy BMI, estimated delivery date based on ultrasound, delivery date). Additional data are obtained from the CGM and wrist-worn PA monitoring device worn by participants, study e-surveys, an electronic scale (for body weight upon waking each day of the study period), and dietary recall telephone interviews to assess eating behavior for one 24-hour period under each treatment (morning PA, evening PA, and no PA). Protected health information is removed from all analytic datasets, and the data sources linked by study ID number. Protected health information required for the conduct of the trial is stored on password-protected servers housed at the University of Tennessee Knoxville and the the University of Tennessee Health Science Center College of Medicine, Knoxville. The de-identified data are pre-processed to make feature types consistent across data sources and to harmonize the multiple data elements.

#### Glucose outcomes

2.5.1

Initially, the participants wore blinded Dexcom G6 CGMs. On 9 December 2024, the IRB approved a modification for unblinded Dexcom G7 CGMs due to the phasing out of the G6. The CGM is placed on the back of the upper arm. The participant is asked to use the side on which they were least likely to sleep for CGM placement (i.e., to avoid compression lows). All CGM data are accessed via Dexcom’s Clarity system.

Glucose outcomes include the mean, area under the curve (AUC), and coefficient of variation (CV) for 24-hour glucose, daytime glucose, and nighttime glucose; percentage of time in range (TIR), percentage of time above range (TAR), and percentage time below range (TBR) were added after the trial was underway. For 24-hour glucose, the start times will vary by treatment; specifically, 24-hour summaries are anchored (begin at) at 4 a.m. for morning PA days, 3 p.m. for evening PA days, and midnight on no PA days. The daytime window is defined as 6 a.m. to 11:59 p.m., and the nighttime window as 12 a.m. to 5:59 a.m (31). Glucose outcomes also include the mean, AUC, and CV for the pre-breakfast (calculated for the 120 min prior to the start of breakfast) and all post-meal periods (calculated for the 120 min after the start of breakfast, lunch, and dinner). The identification of the *time* of the start of breakfast, lunch, and dinner is described in Section *Dietary intake and meal times*.

#### Device data processing and cleaning

2.5.2

Physical activity and sleep are assessed using ActiGraph’s (now Ametris’) CentrePoint Insight Watch. The Watch data are downloaded from ActiGraph’s (now Ametris) CentrePoint system, a cloud-based platform designed to manage and analyze physical activity and sleep data. The de-identified raw (32 Hz sampling rate) device data are exported as 1-second epochs and raw CSV files and read into RStudio. The device sensor data are first examined for wake and sleep times. Sleep time and non-sleep time are defined using participant sleep diaries. Next, the non-wear time is identified using the Choi algorithm (36–38). Days with less than 600 min of non-sleeping wear time will be excluded from the analyses.

#### Device-assessed physical activity

2.5.3

Wrist-specific two-regression algorithms are used to calculate the metabolic equivalent of task (MET) and coefficients of variation (CV) for each time-stamped 1-second, non-sleep period (39). MET values are used to define movement intensity as sedentary (≤1.50 MET), light (1.51 MET–2.99 MET), moderate (3.00 MET–5.99 MET), or vigorous (≥6.0 MET), and the 1-second periods are then collapsed to the minute level (i.e., the average MET value for each minute determined). The total minutes spent in sedentary, light, moderate, and vigorous intensity activity are summed at the day level and for the periods used to categorize the glucose data (i.e., daytime, nighttime, for 120 min before the start of breakfast, and for 120 min after the start of the breakfast, lunch, and dinner).

The data are also used to estimate the activity type, which is designated as continuous walk/run, intermittent, or sedentary activity. First, the MET values assigned to each 1-second non-sleep period are used to identify sedentary activity (≤1.50 MET). Then, 1-second non-sleep, non-sedentary periods with CV ≤21.2% for devices worn on the right wrist or CV ≤19.4% for devices worn on the left wrist are designated as continuous walk/run activity, and those with CV >21.2% for devices worn on the right wrist or CV >19.4% for devices worn on the left wrist are designated as intermittent activity. Continuous walking/running activity is further classified as light-, moderate-, or vigorous-intensity (39). The total minutes of continuous walking/running activity is then summed for the day level, and the periods used to categorize the glucose data.

#### Device-assessed sleep

2.5.4

After the start of the trial, device-assessed sleep metrics were added as secondary outcomes. After identifying “sleep times” from the self-reported diaries, the Cole–Kripke sleep algorithm (40) is applied to obtain sleep metrics that included sleep duration, sleep efficiency (defined as the total percentage of algorithm-detected sleep within the diary-defined sleep window), total waking time during the sleep window, and nap duration.

#### Study e-surveys

2.5.5

Study data are collected and managed using the REDCap electronic data capture tools hosted at the University of Tennessee Health Science Center. Each morning, participants receive a text message with a link to a *Daily Sleep Survey* to complete upon waking. The *Daily Sleep Survey* includes a modified version of the Pittsburgh Sleep Quality Index [PSQI (41)] with questions pertaining specifically to sleep the night before (as opposed to usual sleep habits during the past month, as in the original PSQI). The *Daily Sleep Survey* assesses the time they went to bed the night before, the time they fell asleep, the time they woke up for the day, the number of times they woke up during the night (e.g., to go to the bathroom), the quality of their sleep the night before (i.e., very poor, poor, fair, good, or very good), use of medication to help with sleep, the presence of a bed partner, whether they had trouble sleeping, and the reason they had trouble sleeping (i.e., could not get to sleep within 30 min, had to get up to use the bathroom, could not breathe comfortable, coughed or snored loudly, felt too cold, felt too hot, had pain, other—please describe). The *Daily Sleep Survey* also assesses (i.e., for the day before), napping, whether or not they completed their assigned PA, periods when the CentrePoint Insight Watch was removed, and whether they experienced an injury or accident. *A priori* metrics of interest included the duration (length in hours and minutes) of sleep, sleep efficiency (percentage of time spent asleep while in bed), and sleep quality (i.e., very poor, poor, fair, good, or very good).

Participants additionally complete a *Daily Meal Times Survey* each evening to collect data on the exact times they started breakfast, lunch, and dinner that day.

On the days PA is assigned, participants are texted a link to a *PA Mood Survey* and complete it within 2 h of completing their PA. The *PA Mood Survey* includes questions on the circumstances of PA (e.g., walking, stepping, or a combination of the two; outside, indoors, or both; while listening to music or watching a video), as well as their self-reported mood state during PA. Mood state is assessed using a short version of the Multi-Dimensional Mood Questionnaire (42). Specifically, questions on the extremes of energetic arousal (43), which range from energetic (positive) to worn-out (negative), are assessed using a 6-point Likert scale. Two items assess the extremes of the energetic arousal scale (i.e., during my walking, I felt “energetic” or “worn-out,” each on a 6-point scale representing “definitely not” to “extremely”).

To aid with adherence and minimize recall times and bias, at the Study Visit, participants are asked for their preferred times, within the study’s prescribed window, to complete the *Daily Sleep Survey*, *Daily Meal Times Survey*, and the *PA Mood Surveys*, and the survey schedule is set up accordingly.

At the beginning of the study period, participants are emailed a link to an asynchronous *General Survey*. Participants have the entire study period to complete the *General Survey* (i.e., they can stop at any point and pick back up where they left off at a later time). The *General Survey* assesses demographic characteristics, medical and reproductive history, symptoms of depression (i.e., using the Patient Health Questionnaire (PHQ-9), but excluding the item assessing suicide ideation (44)), the Risk Perception Survey for Developing Diabetes (RPS-DD (45)), and health behaviors, including PA during the month before joining the study, assessed with the Stanford Leisure Time PA Questionnaire (46, 47) and the Pregnancy Physical Activity Questionnaire (48, 49). Smoking and alcohol consumption, and the safety and walkability of their neighborhood are also assessed. Finally, the *General Survey* includes several items pertaining to their preferred time for physical exercise and general circadian preference (i.e., morning vs. evening type) from the Morningness–Eveningness Questionnaire [MEQ (50, 51)].

#### Dietary intake and meal times

2.5.6

Dietary intake is assessed using three 24-hour dietary recalls (24HR) using the United States Department of Agriculture (USDA) five-step multiple pass method (MPM) (52). One 24HR is completed for each treatment condition. Specifically, one of the two days assigned to each treatment condition is randomly selected to determine the 24HR observation day. Participants are called the following day and asked to describe all foods and beverages consumed the previous day. To aid with adherence to the 24HR calls, the activity is highlighted on the participant’s personalized study calendar, and they are asked for their preferred time to conduct the 24HR assessment.

Before beginning the 24HR, a trained research assistant explains the MPM and then obtains the recall data. Two tools are used to enhance the accuracy of self-reported dietary intake data. First, the participants receive a hard copy of a Food Amounts Booklet (FAB) that includes visual images of food and standardized shapes. When applicable, research assistants instruct the participants to reference the FAB to help them quantify the portion sizes consumed. The second tool is an ecological momentary assessment (EMA) platform, which captures pre- and post-photographs of eating occasions in real time. Participants are provided with a unique login and receive detailed instructions on how to upload photographs to the platform (which can be accessed via smartphone device) at the Study Visit. They are instructed to upload pre- and post-photographs of all eating occasions during the observation period. Research assistants access the EMA platform, which displays photographs and associated timestamps indicating when an eating occasion occurred. During the 24HR, research assistants reference the uploaded photographs and prompt participants about omitted food or beverage items to aide in quantifying portion sizes consumed.

Data collected from the 24HR are entered into the Nutrition Data System Software for Research (NDSR; Nutrition Coordinating Center, University of Minnesota, Minneapolis, Minnesota) using version 2022. Variables of specific interest include kcal and grams of carbohydrate, protein, and fat (by eating occasion and by day); glycemic index, glycemic load, available carbohydrate, added sugars, and total sugars (by eating occasion and by day); and the Healthy Eating Index (HEI)-2015 (53) (which assigns a continuous, numerical score based on how well the diet aligns with the Dietary Guidelines for Americans).

The timestamps associated with every photo uploaded, pre- and post, are recorded by two independent research assistants; their data files are then cross-checked against each other and the EMA platform for accuracy. Data on the type of eating episode (i.e., breakfast, lunch, snack, dinner/supper, and beverage) are also obtained from the photo uploads, and similarly double entered and crossed-checked. The timestamps obtained from the uploaded photos will be used to identify the pre-breakfast and all postprandial periods (see Section *Glucose outcomes*). If these data are missing, the *Daily Meal Times Survey* data will be used in their place.

#### Adverse events

2.5.7

No serious adverse events are expected. Potential adverse events include the possibility of skin infection or irritation from the CGM and the risk of injury during the assigned walking or stepping. Adverse events are assessed by participant self-report each morning on the *Daily Sleep Survey* and again, in person by study staff at the Drop-off Visit (when the participants return their equipment and receive their incentives). The trial also has an independent safety officer who advises on the process used to monitor adverse events and is available, as needed, for consultation on the potential need to adjust study procedures for any unanticipated adverse events encountered in the future.

### Incentives

2.6

Participants receive up to $450 in gift cards to Walmart or Amazon as compensation for their efforts at the conclusion of the trial.

### Power and sample size

2.7

Due to the efficiency of the randomized crossover design, sample sizes tend to be small. Power calculations for a repeated measures ANOVA focused on the within-subject effect size. Conservatively assuming that the ratio of effect variance to common variance will be low (i.e., 0.15) and that there will be low correlation across measurements (i.e., 0.15) returns an estimated within-subject effect size of f = 0.73. For this within-subject effect size, with a significance level set at .007 (i.e., Bonferroni adjusted for examination of the seven original glucose outcomes) and a nonsphericity correction of 1, the estimated power was 0.89 for a sample size of 36. Since an enrolled participant could be put on insulin or deliver their baby during the observation period, we set out to recruit and randomize 39 participants.

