This manuscript provides an overview of the Time to Move Randomized Crossover Trial. The Trial’s objective is to compare 30 min of moderate-intensity walking or stepping (30) (i.e., walking in place) under free living conditions, performed either in the morning (i.e., within 30 min to 40 min of starting breakfast) or in the evening (i.e., within 30 min to 40 min of starting after dinner). Previous research by our group suggests that stepping is an acceptable alternative to walking, and given the commonly cited barrier of a lack of time for PA, it may be advantageous in that it can be accomplished while performing other activities that are already part of the everyday routine (30). The primary outcomes include glucose metrics across the 24-hour cycle, assessed using continuous glucose monitors (CGM). We hypothesize that morning PA would improve daytime (6 a.m.–11:59 p.m.) glucose levels, as well as post-breakfast and post-lunch glucose levels, while evening PA will improve post-dinner, nighttime (12 a.m.–5:59 a.m.) (31), and pre-breakfast glucose levels, and thus ultimately improve 24-hour glucose levels. Secondary outcomes include mood during and sleep following bouts of PA. The timing of PA could potentially be leveraged to improve glucose management in this population, thereby leading to improved outcomes for mothers and children.

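### The flat .007 Bonferroni level for seven glucose outcomes is valid, but Holm's step-down test would control the same 5% family-wise error, never reject less, and sometimes reject more

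*Protocol article*

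**What the plan says.** Section 2.7 (Power and sample size) of the protocol article states a "significance level set at .007 (i.e., Bonferroni adjusted for examination of the seven original glucose outcomes"). The calculation is for a single within-subject test: "Power calculations for a repeated measures ANOVA focused on the within-subject effect size". Its other inputs are that "the ratio of effect variance to common variance will be low (i.e., 0.15"), a "low correlation across measurements (i.e., 0.15"), and "a nonsphericity correction of 1". The variance ratio and correlation give an effect that "returns an estimated within-subject effect size of f = 0.73", and the stated power is 0.89 for 36 participants.

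Section 2.8 (Statistical analyses) names repeated measures ANOVA or Friedman's test, followed by linear mixed-effects models. It names no multiplicity procedure, so the .007 in Section 2.7 is the only error-control rule in the article.

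The Background expects effects in many windows. It hypothesises that morning activity would "improve daytime (6 a.m.–11:59 p.m.) glucose levels, as well as post-breakfast and post-lunch glucose levels", and that evening activity would improve the post-dinner, nighttime and pre-breakfast windows and, in the end, 24-hour glucose.

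**The concern.** Read as a decision rule, a flat .007 holds every outcome to .05/7 however many of the others have already been rejected. Holm's procedure orders the p-values and relaxes the threshold after each rejection. It has the same strong family-wise error control under any dependence and needs no added assumption.

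The gain is largest when many hypotheses in the family are false, and that is the situation the Background hypothesises. At stake are real effects in the windows with the larger p-values: they could be reported as non-significant when the same data would support them at the same family error. The point concerns the procedure only, not how many outcomes belong in the family.

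**Working it through.** **Inputs.** All from Section 2.7, except the three conditions (Section 2.3) and the between-outcome correlation:
- seven outcomes, planning level .007
- variance ratio 0.15, correlation across measurements 0.15, nonsphericity correction 1
- three conditions (morning, evening and no physical activity), N = 36
- correlation between outcomes: not given, so assumed 0, 0.5 or 0.8.

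**Step 1: reproduce the plan's figures.**
- Level: 0.05/7 = 0.00714, which is .007 as stated.
- Effect size: f = √0.15 × √(3/(1 − 0.15)) = 0.728, which is 0.73 as stated.
- Power: noncentral F with λ = f² × N = 0.73² × 36 = 19.18 on 2 and 70 degrees of freedom. This gives 0.8875 at .007 and 0.8888 at .05/7, against the stated 0.89.

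The plan's arithmetic is right.

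**Step 2: Holm thresholds.** The j-th smallest of seven p-values is tested at 0.05/(8 − j), stopping at the first failure. The last column is the power of a single F test held at that level.

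| Step | Threshold | Single-test power |
|---|---|---|
| 1 | 0.00714 | 0.889 |
| 2 | 0.00833 | 0.899 |
| 3 | 0.0100 | 0.910 |
| 4 | 0.0125 | 0.923 |
| 5 | 0.0167 | 0.938 |
| 6 | 0.025 | 0.955 |
| 7 | 0.05 | 0.977 |

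Step 1 equals Bonferroni. Every later threshold is looser.

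**Step 3: simulate the family.** Seven correlated three-condition F tests, N = 36, 20,000 trials per setting, with each real effect at the planning size. Average power per true effect, Bonferroni → Holm:

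| Real effects | Correlation 0 | Correlation 0.5 | Correlation 0.8 |
|---|---|---|---|
| 1 | 0.8888 → 0.8892 | 0.8878 → 0.8881 | 0.8867 → 0.8870 |
| 2 | 0.8871 → 0.8962 | 0.8863 → 0.8947 | 0.8890 → 0.8955 |
| 4 | 0.8904 → 0.9213 | 0.8907 → 0.9169 | 0.8891 → 0.9107 |
| 7 | 0.8878 → 0.9700 | 0.8891 → 0.9551 | 0.8884 → 0.9400 |

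Other results from the same simulation:
- Holm lost no Bonferroni rejection in any setting.
- The chance of rejecting at least one of the seven hypotheses was identical under both procedures in every setting.
- With no real effects, the family-wise error was the same under both: 0.0491, 0.0446 and 0.0273 at correlations 0, 0.5 and 0.8. With some real effects, Holm's highest value was 0.0485, still below 0.05.
- With all seven effects real, the chance of rejecting all seven rose from 0.436 to 0.837 (correlation 0), 0.622 to 0.878 (0.5) and 0.737 to 0.907 (0.8).
- With all seven real, the expected number missed per trial falls from 7 × (1 − 0.888) ≈ 0.8 to between 7 × (1 − 0.970) ≈ 0.2 and 7 × (1 − 0.940) ≈ 0.4.

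**The case against.** The strongest case against is that nothing here is wrong. Bonferroni is valid under any dependence, .05/7 is correctly computed, and each outcome already has planned power of 0.89. All of that stands.

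The .007 also sits in the power section, while the analysis section names no multiplicity rule. Sizing at .05/7 is a usual conservative basis for a trial that will be analysed by Holm, and a full analysis plan may name a step-down test. So the article does not firmly commit the analysis to single-step Bonferroni. Even so, the only rule on the page is described as a Bonferroni adjustment for examining the seven outcomes, and a reader would naturally apply it as a flat cut-off.

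Three stronger readings are tempting and are not supported:
- **That Holm beats Bonferroni at every outcome.** It does not. The smallest p-value meets the same .05/7, and any gain depends on other outcomes being rejected first.
- **That power is thrown away for nothing.** Bonferroni gives simple simultaneous confidence intervals, which Holm does not readily give. That is a small but real reason to choose it, although the article does not cite it.
- **That the best case is the expected case.** The Background can be read as naming seven windows, but Section 2.7 does not list "the seven original glucose outcomes", and Section 2.5.1 defines mean, AUC and CV over several periods. Matching the seven outcomes to the seven windows is an inference.

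**Conclusion.** The point holds as a low-cost improvement to a valid plan. For decisions to reject or not, Holm does at least as well as the flat .007 at the same family-wise error, and can do better from the second step on.

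The size depends on how many effects are real: 5 to 8 points of average power if all seven are, 2 to 3 points with four, about 1 point with two, and practically none with one. These figures assume that every real effect has the plan's size, that 36 participants contribute data, and that the between-outcome correlation lies between 0 and 0.8. The sample size and the stated 0.89 need no change.

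**What to change.** Add one sentence to the analysis section: the glucose family is tested by Holm's procedure at a family-wise level of 5%. The smallest p-value is tested at .05/7, the next at .05/6, and so on, stopping at the first failure. Keep .05/7 as the planning level in Section 2.7, so that 36 participants and power 0.89 stand as a lower bound.

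Fix this before unblinding, and preferably before the coded A/B/C results described in Section 2.3 are produced, because the p-value of an overall test across conditions can be read without knowing the labels.

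The change needs no extra participants, data or assumptions. Its cost lies in the intervals. Bonferroni intervals can be shown beside the Holm decisions, with a note that for an outcome rejected only by Holm the interval may still include no difference.
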